As malaria risk may vary between villages, the number of intervention and control households per village will be balanced. A maximum of 10% of all households per village will be enrolled for house screening to avoid the potential diversion of mosquitoes from screened to non-screened households. A similar number of households will be assigned to the control arm in the same village so that the number of intervention and control households will be evenly distributed in each village across the study sites.

The main study outcome will be clinical malaria incidence monitored in the study children cohort by actively following each child enrolled in the study (active case detection-ACD), measuring their body temperature every fortnight for a period of 3–6 months during the high malaria transmission season (January to May) for 2 subsequent transmission seasons of the study. Children presenting with a fever above 37°C or reporting febrile illness in the past week will be tested for malaria using an RDT. The secondary outcome will be parasite prevalence assessed by screening study children at the beginning and end of each transmission season for the 2 consecutive transmission seasons of the study. Vector biting and resting densities indoors will be monitored throughout the study period using CDC light traps and PSC techniques in intervention and control sentinel houses. Acceptability of the proposed intervention, cost of house screening vis a vis LLINs, and the feasibility of scale-up to the community will be assessed using focus group discussions (FGDs) and key informant interviews (KII) with project stakeholders (Fig. 1).

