##### *Entomological endpoints*

The primary entomological endpoint will be the relative indoor mosquito density, expressed as the average number of mosquitoes caught per trap night in each study arm. The secondary endpoint will be the entomological inoculation rate (EIR) incorporating the blood meal source (human biting rate) and the mosquito sporozoite positivity per study arm.

A total of 30 sentinel houses per study arm (*N*=60) per country will be randomly selected for adult mosquito collections. The household selection will be stratified by village and geographical area so that an equal number of sentinel houses are selected in each village and equally spread over the study area. This stratified randomization by the village will reduce the likelihood of imbalances between study arms. Indoor host-seeking mosquitoes will be collected for 5 days each month using CDC UV light traps from 15 sentinel households. The CDC light trap will be placed next to the sleeping space of the study enrolled child and will be raised 1.5 m from the ground. The light trap will be set up at 7:00 p.m. and mosquitoes collected at 7:00 a.m. the next morning.

Indoor resting mosquitoes will be collected using pyrethrum spray catches (PSC) in the remaining 15 sentinel households in each arm of the study. The collections will be done inside the room where the child recruited into the study cohort sleeps. Mosquito sampling using PSC will be conducted early in the morning between 06:00 and 08:00 h. All the exit points to the sleeping area will be shut and a white sheet spread on the floor. An insecticide will then be sprayed in the room to knock down mosquitoes which will then be collected after 10 min. This sampling will be conducted 1 day for each month in the fixed sentinel households throughout the study period.

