##### *Entomological*

House screening is projected to reduce indoor malaria vector collections by at least 50% [51]. We used the *Hayes and* Bennet model for sample size calculation when using means to determine the number of households required to demonstrate a 50% reduction of indoor-entering mosquitoes associated with house screening, with 80% power at the 5% level of significance [50]. A study assessing different mosquito sampling schemes using light traps and human biting catches in Nyimba district, Zambia, in 2014, estimated that 2.6 *An. funestus* were caught using CDC light traps per night [52]. Using Eq. 2 below, we estimated that we would require 17 houses in each arm of the study. An additional 12 households were recruited for mosquito sampling to make a total of 30 households per study arm to allow for sampling of mosquitoes using both the CDC LTs and PSC techniques. Each sampling technique was used to sample mosquitoes from 15 households per study arm. As the standard deviation (SD) for this data was not reported, we assumed a SD of 1.96 for the sample size calculation.

Mosquito data from Chokwe in Mozambique was not available, and there we used the same sample size as that of Zambia of 30 households per treatment arm.
2$$ \mathrm{n}={\left({\mathrm{z}}_{\upalpha /2}+{\mathrm{z}}_{\upbeta}\right)}^2\left({\sigma_0}^2+{\sigma_1}^2\right)/{\left({\upmu}_0\hbox{-} {\upmu}_1\right)}^2 $$

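### Tying each trapping method to 15 sentinel houses per arm leaves light-trap density on fewer houses than the 17 the protocol requires; a monthly exchange of methods would give 30 for the same field work

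*Protocol article*

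**What the plan says.** Trial design {8} gives the general plan: "Vector biting and resting densities indoors will be monitored throughout the study period using CDC light traps and PSC techniques". The Entomological endpoints section sets the number of houses: "A total of 30 sentinel houses per study arm (*N*=60) per country will be randomly selected for adult mosquito collections". It divides them by method. For light traps: "Indoor host-seeking mosquitoes will be collected for 5 days each month using CDC UV light traps from 15 sentinel households". For spray catches: "Indoor resting mosquitoes will be collected using pyrethrum spray catches (PSC) in the remaining 15 sentinel households in each arm of the study", and "This sampling will be conducted 1 day for each month in the fixed sentinel households throughout the study period".

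The entomological part of Sample size {14} confirms the split: "Each sampling technique was used to sample mosquitoes from 15 households per study arm". The same paragraph gives the requirement, worked out from a light-trap catch of 2.6 per night: "Using Eq. 2 below, we estimated that we would require 17 houses in each arm of the study". It explains the larger total this way: "An additional 12 households were recruited for mosquito sampling to make a total of 30 households per study arm to allow for sampling".

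No exchange of methods between houses is described. The statistical methods section plans mixed models that allow for repeated measures within houses and villages.

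**The concern.** Households are the unit of randomization, so the number of independent units behind each mosquito density is the number of houses sampled by that method. That number is 15 per arm per country for each method, although 30 houses per arm have been recruited as sentinels and are visited monthly. For either method, the arm's other 15 sentinel houses contribute nothing.

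The requirement of 17 was computed for light-trap catches, and only 15 houses per arm receive light traps. The figure of 30 looks like a margin over 17 but is not one, because it pools houses measured in two different ways.

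At stake is the precision of the primary entomological endpoint (mean catch per trap night by arm), of resting density, and of the inoculation rate built on these collections. The trial's primary clinical endpoint is not affected.

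**Working it through.** **1. House counts.** Light traps 15 + spray catches 15 = 30 per arm. Stated requirement: 17. The stated build-up, 17 + 12, gives 29, not 30. Fifteen is below 17.

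**2. The protocol's own formula.** Eq. 2 with means 2.6 and 1.3 (50% reduction), SD 1.96 in both arms, 80% power and two-sided 5%:

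n = (1.960 + 0.842)² × 2 × 1.96² / 1.3² = 7.849 × 7.683 / 1.69 = 35.7, so 36 per arm.

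The stated 17 is not reproduced. Three non-standard readings come close: one arm's variance only (17.8), 1.96 taken as the variance (18.2), and Poisson variance (18.1). Fifteen falls short of all of these.

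Treating the house as the unit, as Eq. 2 does, power for a 50% reduction is:

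| Reading of the SD | 15 houses | 30 houses |
|---|---|---|
| 1.96 in both arms | 44% | 73% |
| Halved in the screened arm | 63% | 90% |
| 1.96 is the variance | 72% | 95% |

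**3. Why more nights do not help.** Let vb be the between-house variance, vw the within-house variance, and M the number of monthly rounds. The variance of an arm mean is:

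- fixed houses: vb/15 + vw/(15M)
- monthly exchange: vb/30 + vw/(15M)

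Only the first term changes. With total SD 1.96 and M = 12 (assumed), the ratio of exchange to fixed is 1.00, 0.71, 0.58, 0.54, 0.51 and 0.50 for between-house shares of 0, 0.1, 0.3, 0.5, 0.8 and 1. Under this model the exchange is never worse, and it gains nothing if houses do not differ.

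**4. Light traps on the log scale.** Assumptions: Poisson-lognormal catches, means 2.6 and 1.3, one 5-month season, no baseline adjustment. For an arm with mean μ, house SD σh, night SD σn and n_h nights in house h:

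Var(log arm mean) = 1 / Σ 1/[σh² + ((exp(σn²) − 1) + 1/μ)/n_h]

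The fixed plan is 15 houses × 25 nights. The exchange is 15 houses × 15 nights plus 15 houses × 10 nights. Both total 375 trap nights per arm.

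Example with σh = σn = 0.8. The night term is 0.896 + 1/2.6 = 1.281 (control) and 0.896 + 1/1.3 = 1.666 (screened).

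- Fixed: (0.64 + 1.281/25)/15 + (0.64 + 1.666/25)/15 = 0.0461 + 0.0471 = 0.0932. Power = Φ(0.693/0.305 − 1.96) = 62%.
- Exchange: 1/(15/0.725 + 15/0.768) + 1/(15/0.751 + 15/0.807) = 0.0249 + 0.0259 = 0.0508. Power = Φ(0.693/0.225 − 1.96) = 87%.
- Ratio: 0.0508/0.0932 = 0.545.

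At night SD 0.8 (spray catch: 5 visits against 3 + 2, same mean assumed):

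| House SD | Light-trap ratio | Light-trap power, fixed to exchange | Spray-catch ratio |
|---|---|---|---|
| 0.3 | 0.705 | over 99% in both | 0.887 |
| 0.5 | 0.601 | 93% to 99% | 0.777 |
| 0.8 | 0.545 | 62% to 87% | 0.664 |
| 1.0 | 0.530 | 45% to 72% | 0.620 |

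Over house SD 0.5-1.2 and night SD 0.5-1.0 the ratio is 0.51-0.64 for light traps and 0.56-0.83 for spray catches. Doubling to 10 months barely moves the fixed design (64% and 46% at house SD 0.8 and 1.0), while the exchange reaches 90% and 74%.

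**5. What shrinks the gain.**

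- A simulation with a plain ratio estimator (3,000 runs) gave smaller light-trap gains: 89% to 98%, 56% to 76% and 45% to 59% at house SD 0.5, 0.8 and 1.0.
- A house-by-month effect (assumed SD 0.6-0.8, house SD 0.5, night SD 0.8) moves the light-trap ratio to 0.68-0.72.
- Adjusting for baseline catches from the same houses gives 0.89-0.98 if house effects are perfectly stable, with power above 99% in both designs for house SD 0.5-1.0. With a between-season correlation of 0.5-0.9 the ratio is 0.53-0.81.

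**The case against.** The strongest reply is that fixed sentinel houses are a legitimate design, described consistently in both entomological sections and matched by a mixed model with repeated measures within houses. Sampling starts after the baseline household survey and continues throughout, so fixed houses can act as their own controls. If house effects were perfectly stable, baseline adjustment would remove nearly all the gain. Spray catches also put insecticide into the child's sleeping room, and carry-over into later light-trap catches, possibly different in screened and open houses, is not quantified.

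Much of this stands as qualification. The split is not an internal contradiction, and the model handles the clustering correctly. But a correct model does not add houses, and the baseline argument removes the gain only under perfect stability. It does bear on Zambia and Mozambique, which recruited in 2019: a mid-study exchange there would put each method into houses with no baseline for that method. None of it removes the shortfall of 15 against the stated 17.

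A reader might infer that house differences dominate the error, so that the fixed split discards half the information or leaves the comparison underpowered. The document gives no variance components and does not support that. A halving of variance is the limiting case. With house SD of about 0.3 or less, light-trap power is ample either way and the spray-catch gain is small.

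**Conclusion.** The point holds in a limited form. Each method is tied to 15 houses per arm, and for light traps that is below the protocol's own requirement of 17. The split is explicitly permanent for the spray-catch houses. For the light-trap houses permanence is inferred from the spray catches taking the remaining houses and from the absence of any rotation.

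A monthly exchange would give 30 houses per method at no extra sampling effort, with a variance ratio of about 0.51-0.64 (light traps) and 0.56-0.83 (spray catches). Those ranges rest on the assumed SDs, one 5-month season and no baseline adjustment. The exchange is not a complete remedy: Eq. 2 as printed asks for 36 houses per arm, so 30 would still fall short under that reading. No figure was derived for the inoculation rate. This is an inexpensive improvement to the primary entomological endpoint, worth making where it is still possible.

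**What to change.** In the Entomological endpoints section:

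- **Where sampling has not started** (Zimbabwe was still recruiting): let the two sets of 15 houses in each arm exchange methods every month, on the same calendar in both arms, with the two methods in any one house kept weeks apart. Trap nights (15 × 5 = 75 per arm per month) and spray mornings (15 per arm per month) are unchanged. Keep house as a random effect and add calendar month to the model.
- **In Zambia and Mozambique:** exchange only if the pre-intervention series for each method is not needed. Otherwise keep the fixed houses and state that light-trap density rests on 15 houses per arm, not 17 or 30.

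The cost is a new visit roster and one model term. The downsides are a sparser series per method within each house, light-trap households having to accept spray catches as well (to be covered in the consent for sentinel houses), and possible spray carry-over, which the document does not quantify and which spacing may not fully prevent.

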**Fig. 1 Fig1:**
[figure not shown]
Schematic illustration of trial design

## Methods: participants, interventions, and outcomes

### Study setting {9}

The study will be conducted in three southern African countries: Zambia, Zimbabwe, and Mozambique. Study areas were selected in malaria transmission hotspots where the use of LLINs is promoted by the Ministry of Health, but IRS is not routinely implemented. The project countries had similar profiles in terms of malaria incidence/prevalence, primary malaria vectors, parasites transmitting malaria, vector resistance to insecticides, tools employed in malaria control, and transmission season (Table 1).

**Table 1 Tab1:** Malaria epidemiology in the project countries

Countries	Zambia	Mozambique	Zimbabwe	References
Malaria prevalence/incidence	Prevalence 9% in 2018 for under 5’s.	Weighted prevalence of 38.9% in 2018	Incidence 20.5/1000 population in 2016	[28–30]
Primary vectors	*An. funestus* *An. gambiae* s.s *An. arabiensis* [31]	*An. gambiae* s.l. *An. funestus* s.l.	*An. gambiae* s.l. *An. funestus* s.l.	[28, 32, 33]
Secondary vectors	*An. coustani, An. squamosus, An. pretoriensis* *An. rufipes*	*An. coustani, An. tenebrosus, An. ziemanni.*	*An. coustani, An. natalensis, An. pretoriensis*	[34–38]
Primary parasite prevalence	*P. falciparum* (95%) *P. ovale* (2%) *P. malariae* (3%)	*P. falciparum* (90%) *P.* *malariae* (9%) *P. ovale* (1%)	*P. falciparum* (98%) *P. ovale* & *P. malariae* (2%)	[28, 29, 33]
Insecticide resistance	Both *An. funestus* and *An. gambiae* s.s. resistant to deltamethrin, lambda-cyhalothrin, permethrin and DDT.	Both *An. funestus* s.l. and *An. gambiae* s.l. resistant to deltamethrin, alphacypermethrin, lambda-cyhalothrin, permethrin and DDT in some areas of Mozambique.	*An. arabiensis* reported to be resistant to DDT and permethrin. *An. funestus* was reported to be resistant to carbamates and pyrethroids. *An. gambiae* s.l. reported to be resistant to bendiocarb and lambda-cyhalothrin.	[29, 33, 39]
Malaria control tools	IRS, LLINs, IPT_P_, RDTs, and case management using ACTs [40].	IRS, LLINs, RDTs, case management using ACTs, Social & Behaviour Communication Change (SBCC) and entomological monitoring and surveillance.	IRS, LLINs, RDTs, case management using ACTs, therapeutic efficacy testing (TET), Community-based management of malaria, IPT_P_, and entomological surveillance.	[29, 33, 40]
Transmission season	January–April	January–April	January–April	[28, 30, 33]

### Nyimba, Zambia

The house screening trial will be conducted in the Nyimba District located 350 km East of Lusaka in Eastern Province, Zambia. Nyimba has a cool dry winter from May to August and a warm wet season from December to April, which is the main malaria transmission season [41]. *Plasmodium falciparum* in Nyimba is vectored by *An. funestus* which mediates an entomological inoculation rate (EIR) of 70 infectious bites per unprotected user of LLIN [42]. The average annual temperature is 25°C, and the annual average rainfall was 175 mm from 2009 to 2020 [43] (Fig. 2).

**Fig. 2 Fig2:**
[figure not shown]
Map showing the study area in Nyimba District, Eastern Province, Zambia

### Chiredzi, Zimbabwe

The evaluation of house-screening will be explored in Chiredzi District located in Masvingo province in South-Eastern Zimbabwe situated at 21° 02′ 20′′ S 31° 40′ 40′′ E. Chiredzi district receives on average 78 mm of annual rainfall and has an annual average temperature of 26°C [43]. The main malaria vector found in this area is *An. funestus. An. quadriannulatus* was found to be the most predominant of the *An. gambiae.* s.l. complex. Other anophelines present in the area were *An*. *pretoriensis*, *An*. *squamous*, *An*. *rufipes*, *An*. *coustani*, and *An*. *pharoensis*. The major control measures employed in the area are IRS, LLINs, larval source management (LSM), and prompt case management [44] (Fig. 3).

**Fig. 3 Fig3:**
[figure not shown]
Map showing the study area in Chiredzi District, Masvingo Province, Zimbabwe

### Chokwe, Mozambique

The house-screening trial will be conducted in Chokwe District, Gaza Province, specifically within the study area of the Chokwe Health Demographic Surveillance System (CHDDS), at 24° 33′ 37′′ S, 33° 1′ 20′′ E in southern Mozambique. Chokwe district receives on average 72 mm of annual rainfall and has an annual average temperature of 26°C. The major *P. falciparum* vectors are *An. funestus* and *An. gambiae* s.l. *An. funestus* are recorded to be highly resistant to pyrethroids in Chokwe [45] and as a result, IRS using DDT has been used for malaria control in this area since 2006 [45] (Fig. 4).

**Fig. 4 Fig4:**
[figure not shown]
Map showing study areas in Chokwe District, Mozambique (HDSS study area), in Chokwe District, Gaza Province, Mozambique

### Eligibility criteria {10}

The households to be enrolled in the study will be assigned the following inclusion criteria:
Houses that have either a tin or tiled roof; mud, stone, or wooden walls and earthen or cemented floors (*semi-modern) with few open spaces for potential mosquito entry and screening; the houses should not be in such a debilitated state that it is impossible to cover up the mosquito entry points.Houses are at least 50 m apart to prevent the diversion of mosquitoes from the treatment to control houses.Houses have at least 1 resident child between 6 months and 13 years of age.The resident child recruited into the study cohort will stay in the study area for the whole study period and will not be allowed to travel out of the study area during the project period.Houses in which the household head/guardian has signed the study informed consent.

### Who will take informed consent? {26a}

Once all houses (800) to be enrolled in the study have been identified, consent will be sought from the household heads/guardians for a resident child between 6 months and 13 years, to join the study cohort for the malaria incidence (clinical malaria) and prevalence (parasite density) surveys.

Written and verbal information will be provided to household heads/guardians on the objectives, benefits, and potential risks of the study using a local language with which they are familiar. The household heads/guardians will be advised that participation is voluntary. Only children whose parents have given written consent for their child to be included in the study will be enrolled.

The participant child will be selected randomly among those aged 6 months to 13 years from the 800 houses enrolled. During the blood specimen collection for clinical malaria infection and parasite prevalence, assent will be sought from children above 8 years, and if the assent is denied, this child will be excluded from data collection. No distinctions will be made regarding the gender or ethnic group of the household.

Consent will also be sought from household heads for their houses to be used as sentinel stations for the sampling of adult mosquitoes using CDC light traps and PSC techniques.

Any child testing positive for malaria parasites will be treated as per respective national malaria diagnosis and treatment guidelines [46].

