### Additional consent provisions for collection and use of participant data and biological specimens {26b}

On the actual day of blood specimen collection, the household heads/guardians will be presented with another consent form before a blood specimen is collected from the study children. If consent is obtained, then the field workers will collect the data. However, if consent is denied, blood specimens will not be collected from the child.

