#### Outcomes {12}

##### *Clinical endpoints*

The primary endpoint will be the incidence of clinical malaria in children between 6 months and 13 years. Clinical malaria will be assessed by active case detection over the main transmission season (January-April). The axillary temperature will be taken every fortnight by CHWs from all enrolled study children and if ≥ 37.5°C or history of fever in the past 48 h is reported, the child will be tested for malaria using a rapid diagnostic test kit (RDT). Blood specimens will also be collected using thick and thin blood slide smears for parasite identification and a dry blood spot (DBS) using a filter paper for later malaria analysis using PCR techniques.

The secondary endpoint will be the prevalence of malaria parasitemia in the study children, and the average parasite density in each study arm will be determined. Cross-sectional surveys will be done before (November) and after the main transmission season (May). A finger prick sample will be taken for an RDT and a thick and thin blood smear and DBS prepared for microscopy and molecular analysis in the laboratory.

RDT positive children will be provided with a full dose of *Artemether-lumefantrine* (AL) for treatment by a trained health worker following in-country national guidelines [47].

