##### *Recruitment {15}*

Study participants will be recruited by the national project team in consultation with local health workers. The project staff will obtain verbal and written informed consent using ethical review committee (ERC)-approved language that outlines the objectives, benefits, and potential risks of the study and the data and biological samples that will be collected. Household heads will be briefed about the study, provided with an information sheet, and asked for their written consent to have their children involved in the study. Assent will be sought from all children above the age of 10 years. Household heads/guardians who do not want their children to participate in the study will be free to refuse participation. On the survey day, children will be informed about the survey procedures, making it clear that their participation is voluntary and that they might opt-out at any time if they chose to. Children unwilling to participate or whose parents did not give consent will be excluded from the selection procedure, with assent obtained from selected children before samples are collected. Participants’ names will be removed from the final database to ensure anonymity. Children with a positive malaria RDT will be treated for malaria according to national guidelines.

Participants will be free to withdraw from the study at any time without giving a reason. In the unlikely event that homeowners require their house to be returned to the pre-intervention state, items added will be removed. No replacements will be made during the surveillance period in either year, but in year 2, children who have withdrawn or are no longer in the study for any reason will be replaced by a child within the age range of 6 months—13 years in the same household. If another child within this age range is not present in that house, then another household with a child within this age range will be sampled in the same village. If a household withdraws consent, no further follow-up will be made in that household. All data collected up until the point of withdrawal will be kept for the per-protocol analysis at the end of the study. If the house was participating in the entomology collections, it will be replaced by a neighboring house of the same type and intervention status.

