##### *Plans to promote participant retention and complete follow-up {18b}*

Once a household and child are enrolled or randomized, the study team will make every reasonable effort to follow the child for the entire study period.

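### The rule on refused assent can be read as ending a child's follow-up at a suspected malaria case; it should be aligned with the rule for guardian refusal and the retention commitment

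*Protocol article*

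**What the plan says.** Four parts of the protocol article bear on this.

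- **Who will take informed consent? {26a}**, on blood collection for both clinical malaria and parasite prevalence: those older than 8 are asked for assent, with this consequence: "if the assent is denied, this child will be excluded from data collection".
- **Additional consent provisions {26b}**, on the guardian's decision on the same day: "if consent is denied, blood specimens will not be collected from the child". No wider consequence is stated.
- **Plans to promote participant retention {18b}**: the commitment, covering everyone taken into the trial, is that "the study team will make every reasonable effort to follow the child for the entire study period".
- **Trial design {8}**, on when blood is requested for the primary endpoint: "Children presenting with a fever above 37°C or reporting febrile illness in the past week will be tested for malaria using an RDT". The Clinical endpoints text under Outcomes {12} sets a different trigger (axillary temperature of at least 37.5°C, or fever reported in the preceding 48 hours). Under both, testing follows fever or reported fever.

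Households are the randomized unit, with one child followed in each. The blinding section says that families and data collectors will know the allocation.

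**The concern.** The same refused finger prick has two stated consequences, depending on who refuses. If the guardian refuses, a specimen is missing. If an older child refuses, the wording takes the child, not just the specimen, out of data collection.

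In active case detection a refusal can occur only at a visit where malaria is already suspected. If field teams follow the assent sentence literally, follow-up of an older child in a randomized household ends at a suspected event. Missing data would then depend on the outcome, in a trial where families know their arm. The sentence also covers the cross-sectional surveys, so on the same reading a refusal at the pre-season survey would remove a child from the primary-endpoint follow-up as well.

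**Working it through.** **Inputs from the protocol article.** Sample size {14}, Zambia: control rate λ0 = 0.312 per child from January to June, 35% reduction (λ1 = 0.65 × 0.312 = 0.2028), 80% power, 5% significance level, 338 required and 400 recruited per arm.

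**Reproducing the plan's figure.** Equation 1 with z values of 1.96 and 0.84: 2.80² × (0.312 + 0.2028) / (0.1092)² = 338.5 (338.8 with unrounded z), against 338 stated. For Mozambique (0.325) it gives 324.9, against 324. Both reproduce. Power at 400 per arm with no loss (Zambia): Φ(0.1092 / √(0.5148/400) − 1.96) = Φ(3.044 − 1.96) = 86.1%.

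**Assumptions, since the documents give no refusal rate or age distribution.**
- Ages uniform from 0.5 to 13 years, so the share above 8 is s = 5/12.5 = 40%.
- A fraction r of true cases in these children meets a refusal, with r = 5–20%.
- Literal reading: the case is unrecorded and the child's follow-up for that season ends. With a constant rate λ, the mean fraction of the season observed in older children is E = (1 − e^(−λr)) / (λr).
- Recorded rate = [(1 − s)λ + sλ(1 − r)E] / [(1 − s) + sE].

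**Equal refusal in both arms, 400 per arm.** The last column keeps the child in follow-up (E = 1) but still loses the untested case.

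| r | Rate ratio | Control cases lost, of 124.8 | Power, literal reading | Power, specimen only |
|---|---|---|---|---|
| 5% | 0.650 | 2.9 | 85.3% | 85.4% |
| 10% | 0.650 | 5.7 | 84.5% | 84.7% |
| 20% | 0.650 | 11.2 | 82.8% | 83.1% |

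Most of the lost cases are the untested episodes themselves: 124.8 × 0.4 × r = 2.5, 5.0 and 10.0.

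**Refusal 10 points higher in one arm.** Ignoring the small change in person-time, with 10% against 0%:
- Higher in the intervention arm: 0.65 × (1 − 0.4 × 0.10) = 0.62.
- Higher in the control arm: 0.65 / (1 − 0.4 × 0.10) = 0.68, with power 77.8%.
- With a true ratio of 1.00, the observed ratio is 0.96 or 1.04.

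**What rewording recovers.** The model above counts refusals at true cases only. Under the literal reading a refusal at any febrile visit ends follow-up. Assuming 0.5–0.9 febrile visits per child-season and 5–10% refusal, the share of older children lost per season is 1 − e^(−0.05×0.5) = 2.5% to 1 − e^(−0.10×0.9) = 8.6%. Multiplied by 0.4, that is 1.0–3.4% of the cohort.

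**The case against.** The strongest reply is that the article never says the child leaves the cohort. The assent sentence is set in the context of specimen collection, and the neighbouring section on guardian consent uses data and blood specimens almost interchangeably. Withdrawal is treated separately under Recruitment {15}. On this reading the sections agree. The reading is available and stands as an objection to any claim that permanent exclusion is stated. It does not settle the matter: the wording excludes the child, and teams in three countries would have to choose an interpretation.

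Other parts of the reply also stand:

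- The rule covers only children asked for assent. A reader might apply 5% against 15% refusal to every febrile visit and infer a ratio of 0.58 or 0.73 (0.65 × 0.85/0.95 = 0.582; 0.65 × 0.95/0.85 = 0.726). That does not measure a rule limited to older children.
- A reader might infer that a child excluded midway through the first season costs three quarters of the planned visits. Recruitment {15} allows replacement in year 2 from the same household where possible; the household would then lose about one quarter.
- Blood cannot be taken without assent, so the untested episode is lost under any wording. Dropping that visit from the denominator would remove almost none of the bias.
- How untested febrile visits are counted or imputed is commonly left to an analysis plan, which is not shown. Its absence here is no fault.
- Nothing in the documents shows that refusal differs by arm, and bias in the ratio depends on that.

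**Conclusion.** The point holds as an unreconciled rule with a modest effect. The assent sentence conflicts in its literal sense with the guardian-refusal rule and with the retention commitment, and for the primary endpoint it operates only at suspected cases. Equal refusal leaves the rate ratio unbiased and power at about 83–85%. A 10-point difference between arms moves 0.65 to about 0.62 or 0.68. These figures rest on assumed refusal rates, a 40% share of older children, a constant rate and Zambian incidence. The share is itself uncertain: {26a} asks assent above 8 years, while Recruitment {15} says "Assent will be sought from all children above the age of 10 years", which under the same uniform ages gives 3/12.5 = 24% and smaller effects.

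The documents do not support the stronger conclusion that children are permanently removed, or that rewording would cure the bias from differential refusal. What rewording prevents is the additional loss of later visits, tests and surveys after a refusal, which is avoidable and would otherwise weaken the intention-to-treat comparison.

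**What to change.** Reword the sentence in {26a} to match {26b} and {18b}: refusal by child or guardian forgoes only that day's specimen. The child stays in temperature checks, later tests, the cross-sectional surveys and the intention-to-treat set unless the family withdraws from the study. Record each refused test at a febrile visit and report the counts by arm, so that differential refusal can be seen. In the same edit, reconcile the two assent ages and the two fever triggers.

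The core change costs one sentence and one field in the electronic form. The right to refuse is unchanged. The article reports recruitment still under way in Zimbabwe, so the clarification can take effect there; in Zambia and Mozambique, refusals to date can be reported as far as they were recorded.
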